# Effectiveness of an interactive web-based health program for adults: a study protocol for three concurrent controlled-randomized trials (EVA-TK-Coach)

**DOI:** 10.1186/s13063-021-05470-8

**Published:** 2021-08-10

**Keywords:** Primary prevention, Health behavior, Healthy lifestyle, Smoking cessation, Physical fitness, Weight loss, Randomized controlled trial, Internet based intervention, Web-based health program, Behavior change

## Abstract

**Background:**

A healthy lifestyle can help prevent diseases that impair quality of life and lead to premature death. The *Techniker health insurance fund* offers a comprehensive online health program to support users in achieving their health goals of *Increasing Fitness*, *Losing and Maintaining Weight*, or *Smoking Cessation*.

**Methods:**

The aim of this study is to test the long-term effectiveness of the web-based *TK-HealthCoach* with regard to the primary outcomes of increased physical activity, sustainable weight reduction, and smoking abstinence. We are conducting three interconnected, randomized controlled trials (RCT), one for each health goal, within which participants are allocated to an intervention group (interactive online health program) or a control group (non-interactive online health program).

The effects of the intervention groups compared to the control groups will be analyzed by multi-level models for change. Participants’ data are captured via online questionnaires before the program starts (baseline t0), again when it ends (t1), and later at two follow-up surveys (t2 and t3); the latter 12 months after t1. We are documenting socio-demographic, health-related, and psychological variables as well as usage behavior data of the programs.

According to our sample size calculation, we have to enroll 1114 participants in each *Losing and Maintaining Weight* and *Increasing Fitness* RCT and 339 participants in the *Smoking Cessation* RCT. Additionally, 15–20 participants in the interactive smoking-cessation program will be invited to qualitative telephone interviews with the aim to obtain detailed information concerning utilization, compliance, and satisfaction.

The online RCTs’ inclusion criteria are: adults of each gender regardless of whether they are insured with *Techniker health insurance fund*. Persons with impairments or pre-existing conditions require a medical assessment as to whether the program is suitable for them. Specific exclusion criteria apply to each program/RCT.

**Discussion:**

We assume that study participants will improve their health behavior by using the offered online health programs and that each health goal’s intervention group will reveal advantages regarding the outcome variables compared to the control groups. Study enrollment started on January 1, 2020.

**Trial registration:**

German Clinical Trials Register, Universal Trial Number (UTN): U1111-1245-0273. Registered on 11 December 2019

**Supplementary Information:**

The online version contains supplementary material available at 10.1186/s13063-021-05470-8.

## Background

Consumer habits and working conditions strongly influence each member of society’s lifestyle. Smoking, low physical activity and obesity lead to increased individual health risks, e.g., for cardiovascular diseases, cancer, diabetes mellitus, musculoskeletal diseases, etc., putting a very high financial burden on the healthcare system. Recommendations have been made globally and programs developed to support a healthy lifestyle [1–3]. The earlier a healthy lifestyle is implemented, the less likely one is to suffer from the consequences of tobacco consumption, low physical activity, or obesity. However, lifestyle changes are particularly hard to realize when disease-related burdens are not yet apparent. Moreover, people free of cardiovascular diseases but carrying risks like smoking, hypertension, diabetes mellitus, and obesity who initially took statins or antihypertensive drugs decreased physical activity and increased weight, as Korhonen et al. found in their cohort study with > 41,000 participants [4].

Digital programs promoting primary prevention can play an important role for working-age adults. There are already many commercial and non-commercial online programs to support preventive health behavior, although the variety on offer is immense, as is their quality [5]. Some online programs were tested in randomized-controlled trials, but as their content, duration, and possibilities of interactivity differed, the effectiveness varied widely. However, results show that the more individualized and interactive online interventions are aligned, the stronger are their effects [6–13]. Nevertheless, we must keep in mind that strong interactivity and close ties to a web-based program may also make participants feel overly obliged, which may cause users to quit the program prematurely. Particular motivational and volitional factors for changing health behavior are therefore very important [14, 15]. The content of an E-Coach, its individual usability and degree of interaction, and its technical functionality and design are playing an important role to encourage user’s program adherence and thus a successful change in behavior [14].

Digital health services are often highly commercialized, and there is a myriad of health programs of very different quality offered by commercial and non-commercial institutions and health insurers. It is difficult for users to assess the effectiveness and security of the programs. Ineffective health programs are not only unnecessarily costly—they may also cause harm or demotivate participants sustainably.

It is therefore necessary to ensure that such digital applications make their benefits and effectiveness transparent to potential users [16–18]. Furthermore, scientific and comparable quality criteria should be developed to support both customers and health care providers choose or offer effective digital health programs.

To improve disease prevention, the German *Techniker (TK) health insurance fund* developed, with support from experts in medicine, sports science, psychology, and motivational psychology, a comprehensive online health coach to encourage users to achieve individual health goals. Three of these health goals—*Increasing Fitness*, *Losing and Maintaining Weight* and *Smoking Cessation*—will be independently examined by the Section of Health Care Research and Rehabilitation Research (SEVERA) and Medical Center Freiburg and the Department of Sport and Sport Science (IfSS)—both located in the University of Freiburg.

SEVERA is mainly responsible for coordinating the overall study and its summative evaluation, which is being carried out via three online randomized controlled trials (RCTs) (one for each health goal). It is also responsible for the formative evaluation of the intervention and control group programs with the *Smoking Cessation* health goal.

The IfSS is responsible for two substudies conducting sports and nutritional medical examinations of participants living in the postal code area 79 (South Baden). The protocol of these substudies will be published separately. The IfSS will also evaluate the usage behavior data from the *Increasing Fitness* and *Losing and Maintaining Weight* programs.

## Methods/design

### Study aim, design, and setting

The aim of this study is to test the long-term effectiveness of the *TK-HealthCoach* with regard to these primary outcomes: increased physical activity, weight loss, and smoking abstinence. An online randomized controlled trial (RCT) of parallel design is being conducted as part of the summative evaluation for each of the three health goals *Increasing Fitness*, *Losing and Maintaining Weight*, and *Smoking Cessation*. The aim is to examine if participants of interactive online programs achieve higher effects on study outcomes than participants of non-interactive programs.

Adults across Germany intending to lose weight, increase their fitness or quit smoking are invited to participate in one of the online studies. We are planning to recruit a total of approximately *N* = 2567 participants in the three online RCTs. In addition to these online RCTs, the Department for Sport and Sport Science (IfSS), University of Freiburg is conducting two medical substudies on the health goals *Increasing Fitness* and *Losing and Maintaining Weight*. The aim of these two substudies is to determine long-term physiological effectiveness as a result of behavioral changes. Since the precondition for participating in either substudy is to fill out the online questionnaires, the total number of participants to be recruited has to increase by *n* = 336 to *n* = 2903 (sample size calculation see Table 5).

Formative evaluations will be conducted in addition to the *TK-HealthCoach’*s summative evaluation. These include (a) detailed quantitative analyses of usage behavior data and (b) qualitative interviews with persons participating in the intervention group of the online RCT *Smoking Cessation*.

Study period of each RCT includes the program runtime of the health goals (*Smoking Cessation*: six weeks; *Increasing Fitness* and *Losing and Maintaining Weight*: 12 weeks) as well as another twelve-month follow-up after the program’s completion.

Participant data is being captured via online questionnaires at these time points:
Baseline t0: after registration and before the program startsFollow-up t1: after completing the program
*Smoking Cessation*: after 6 weeks*Increasing Fitness* and *Losing and Maintaining Weight*: after 12 weeksFollow-up t2:
*Smoking Cessation*: 4 months after completing the program*Increasing Fitness* and *Losing and Maintaining Weight*: 6 months after completing the programFollow-up t3: 12 months after completing the program in all three RCTs.

The data on program usage will be recorded during the entire study period.

In the RCT *Smoking Cessation* qualitative telephone interviews will be carried out once the t1 questionnaires have been completed.

### Research questions and hypothesis

The following questions and hypotheses are being investigated in this study
What effects do the online programs within the three health goals *Losing and Maintaining Weight*, *Increasing Fitness*, and *Smoking Cessation* have on the primary and secondary outcomes variables reported by participants?We assume that we will observe statistically significant improvements with small to medium effect sizes for each program.Will the intervention groups (interactive health programs) in each RCT reveal stronger effects on primary and secondary outcomes in comparison to the control groups (non-interactive health programs)? We will test the hypothesis that the intervention groups’ changes in the primary and secondary outcomes are more positive than the control groups’. Our focus is on long-term effects so we will analyze the change between baseline (t0) and 1 year after the intervention finishes (t3), while short-term effects are part of the secondary analyses. We expect small to medium effect sizes from the comparison between these two groups.Does the intensity of use of health programs have an impact on their effects?The hypothesis we test is that study participants who use their health program more frequently and intensively achieve better outcomes than study participants who use the program less often or less intensively.How satisfied with the programs offered are the study participants in the intervention- and control groups? This question will be examined exploratively in secondary analyses.

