### Recruitment procedure

From January 1 to 17 of June 2020, a total of *N* = 2903 study participants have to be recruited in all RCTs, including the local medical substudies. The number of participants who have to be enrolled in the online studies is N = 2567.

Recruitment activities and information are being disseminated via online and print media. These include various information provided via channels of the *TK health insurance* (websites, newsletters, blogs etc.), advertisements on Google, and different health media. Advertisements in the local press and radio, the intranet of the University of Freiburg and its Medical Center, and a local display of flyers serve to recruit specifically for the regional medical substudies.

People intending to change their health behavior find brief information about the study and its objectives on the project’s homepage. As specific inclusion and exclusion criteria apply to each of the three programs or RCTs respectively, detailed study information is provided on each program entry.

If interested persons give their informed consent to participate in the program and study, and after completing their registration, they will as participants receive the first health goal-specific questionnaire by e-mail (baseline t0).

Participants in the *Increasing Fitness* or *Losing and Maintaining Weight* RCTs living in the postal code area 79 are offered the possibility to enroll in the medical substudies after filling out the t0 questionnaire. These substudies entail sports and nutritional medical examinations (details will be published in the study protocol of the medical substudies).

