## Interventions

All study participants are given access to a health goal-specific, web-based online program with the difference being that the intervention group is offered a comprehensive, interactive program and the control group a less extensive, non-interactive program.

All participants have access to a personal profile page where they find their personal registration data, study information, and declaration of consent as well as the possibility to unsubscribe from the study and/or program.

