Possible covariates (see Table 4) will enter the model at level 1 (X) when they are measured at more than one time point or at level 2 (Z) when they are only measured at baseline. The covariates differ in type and number between the three coaches. The components X and Z are therefore only placeholders. The covariates considered may represent real-life conditions of participants existing independently of the program; they can be beneficial or detrimental to participants’ goal attainment or outcomes. The social environment in particular may be conducive or an obstacle [26–30]. The importance of social and emotional support from people, who are close, is also pointed out by the NICE guideline *Behaviour Change: individual approaches* [31]. Tiredness and a decrease in drive and activity are indications of mood disorders. Self-efficacy, motivation and intention to change, as well as functional or physical limitations are predictors for behavioral change and associated with mental health, health status, and comorbidities [32–40]. Furthermore, it is likely that additional addictive behaviors and low degree of mental health will make smoking cessation more difficult [33, 41, 42]. Since past behavior predicts future behavior, as confirmed in a meta-analysis [43], preconditions such as mental health, health status comorbidity, additional addictive behavior, but also social support, assessed at baseline, are considered as program-independent covariates of primary outcomes. We use these covariates, along with sex, age, and primary outcome at baseline to adjust the statistical models in the analyses. In these models, coefficient *γ*_10_ refers to the change over time of the intervention groups (hypothesis 1), while coefficient *γ*_11_ refers to the difference in change between intervention and control group (hypothesis 2).

For the analyses of secondary outcomes, measuring mean changes over time (see Table 3), we use linear mixed models analogous to the primary outcomes in weight loss and fitness. Differences between intervention and control groups in for example “Health related goal intention” or “Perceived goal attainment” will be analyzed using *t* tests.

To test the dose-effect association (hypothesis 3), the outlined model will be adapted—here, we only use the intervention group, so the group variable will be dropped. Instead of the group variable, a variable that code the use (e.g., number of logins) of the coach will enter the model at level 2.

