### Trial status

Protocol version number 3; date of approval: 2019 July 25 (amendment: 2019 October 28).

Study enrollment began on January 1, 2020. After the first 6 weeks, we noticed that the *Losing and Maintaining Weight* health goal was chosen much more often than the *Increasing Fitness* health goal. As we had expected, recruitment for the *Smoking Cessation* health goal was continuous and good. We therefore tried to draw more attention to the *Increasing Fitness* health goal by adjusting keywords and budget of the online ads.

In line with our study’s risk management, we consider that, as studies involving digital interventions and digital surveys are notorious for encouraging a rather low level of personal commitment, the risk of program drop-outs or study discontinuations is higher than in trials involving personal, face-to-face contacts [45, 46]. In addition, common technical problems on the part of the provider or user can increase dropout rates. For these reasons, individuals interested in the study and its participants are able to contact the participating institutions by phone and/or e-mail to obtain personal advice. Nevertheless, the dropout rate could exceed the estimated 50% rate associated with all online RCTs. Dropouts could occur if participants are dissatisfied with the programs or in case of unpredictable events such as the rapid spread of the coronavirus in Germany since March 2020 and potential problems associated with general high attention, the health of participants, technical problems due to the congestion in the internet, etc. Therefore, we are monitoring the response rates at t1 and, if necessary, will raise the number of participants to be recruited. We closed recruitment on 05 October 2020.

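### In the fitness and weight trials, research question 1 asks for program effects but is answered by an uncontrolled within-arm change, which can only be descriptive

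*Protocol article*

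**What the plan says.** Under Research questions and hypothesis, the first question begins "What effects do the online programs within the three health goals" and its stated expectation is "We assume that we will observe statistically significant improvements with small to medium effect sizes for each program". The comparison of interactive with non-interactive programs is a separate, second question.

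Under Summative evaluation, each question is tied to a coefficient of the mixed model. γ10 "refers to the change over time of the intervention groups (hypothesis 1"), and γ11 "refers to the difference in change between intervention and control group (hypothesis 2"). Time enters as four points coded 0 to 3. The basic model names no calendar or season term.

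Under Interventions, "All study participants are given access to a health goal-specific, web-based online program": the intervention arm gets the interactive version and "the control group a less extensive, non-interactive program". No arm is without a program.

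The Recruitment procedure section describes who enters: "People intending to change their health behavior find brief information about the study". The Study aim section likewise invites adults who intend to lose weight, become fitter or stop smoking. Trial status gives enrollment as 1 January to 5 October 2020 and lists "unpredictable events such as the rapid spread of the coronavirus in Germany since March 2020" among possible causes of dropout. It does not mention it as an influence on the outcomes.

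**The concern.** The first question is causal, but the coefficient assigned to it is a before-after change. Randomization protects γ11 only. γ10 collects everything that moves the outcome over the follow-up: the program, the natural course in people who have just resolved to change, regression to the mean, season and calendar events. Since both arms use a program, the trial observes no course without one that could be subtracted.

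This does not depend on which arm is coded 0, because the slope of either arm alone is uncontrolled.

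At stake is the reading of the first-listed research question. Followed as written, a significant within-arm improvement would count as an effect of that program, even if interactive and non-interactive versions did equally well for reasons unrelated to either. Drift in the unfavorable direction could equally hide a real benefit. The article's Background argues that program effectiveness should be made transparent to users, so the distinction matters to the people who will read the result.

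**Working it through.** **1. The plan's own figure.** Inputs from Table 5: between-arm effect size 0.25, two-sided α 0.05, power 0.80.

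- Normal approximation: n = 2(1.960 + 0.842)² / 0.25² = 251.2, so 252 per arm. The t-test version gives 252.13, so 253, as stated.
- Dropout of 50%: 253 / 0.5 = 506 per arm. Total 1012 × 1.1 = 1113.2 (stated 1114).
- Footnote 3 of Table 5 carries the same 253 to the weight trial.

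The sample size therefore rests on the randomized contrast. Nothing below changes it.

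**2. Calendar.** Inputs: 12-week program, t3 12 months after program end, enrollment 1 January to 5 October 2020.

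- t0 to t3 is 12 weeks plus 12 months, about 14.8 months, so t3 falls about 12 weeks later in the year than t0.
- Entry 1 January 2020: t1 on 25 March 2020, t3 on 25 March 2021.
- Entry 5 October 2020: t1 on 28 December 2020, t3 on 28 December 2021.
- Entrants in January and February 2020 have a baseline before the pandemic and, since the earliest t1 is 25 March 2020, all follow-up within it. Entrants from March 2020 have both ends within it.

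In the smoking trial the interval is 6 weeks plus 12 months, about 13.4 months. The analysis there drops t0.

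**3. How little drift gives significance (illustration).** Neither a drift nor a t0–t3 correlation r is given in the documents; both are assumed. A paired t0–t3 change in completers stands in for the mixed-model slope. In units of the outcome SD:

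SE of mean change = √(2(1 − r)/n), with n = 253.

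- r = 0.5: SE = √(1/253) = 0.063; observed shift for p = 0.05 is 1.96 × 0.0629 = 0.123.
- r = 0.7: SE = √(0.6/253) = 0.049; observed shift 0.095.

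Chance that the within-arm test is significant with no program effect, Φ(shift/SE − 1.96):

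| True drift (SD) | r = 0.5 | r = 0.7 |
|---|---|---|
| 0.10 | 36% | 54% |
| 0.15 | 66% | 87% |
| 0.20 | 89% | 98% |

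A true drift equal to the threshold (0.123 at r = 0.5) would be significant in about half of trials. In 20,000 simulated trials with a common drift in both arms (0.10, 0.20 and 0.25 SD of the change score, which equals the outcome SD at r = 0.5), the between-arm test rejected in 4.8% to 4.9%.

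**4. Cancellation of season.** Assume uniform entry over the 278 days and a sinusoidal yearly pattern. The average 12-week shift is then at most sin(x)/x of the largest individual shift, with x = π × 278/365.25 = 2.391. This gives 0.682/2.391 = 0.285. A mean seasonal drift of 0.20 SD would need individual shifts of about 0.20/0.285 = 0.70 SD, and 0.123 SD would need about 0.43 SD.

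**The case against.** The strongest reply is that the article already rests effectiveness on the randomized comparison. The Study aim section says the aim is to see whether interactive programs do better than non-interactive ones, the Discussion says effectiveness is analyzed by comparing the arms, and Table 5 is sized for that contrast. Question 1 speaks only of an assumption, whereas question 2 announces a test. This stands as far as it goes: the main comparison is sound, and a reader should not infer that the trial cannot show effectiveness. It does not remove the mismatch, because question 1 still asks for effects, predicts statistical significance and is assigned a coefficient, with no limit on its interpretation.

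Four stronger readings are tempting and are not supported:

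- **That the smoking trial counts any quitter as improvement over a baseline of smokers.** The Summative evaluation section drops t0 for that reason and uses the between-group difference as the effect size.
- **That a 15-month t0–t3 change is the planned test of question 1 in all three trials.** The interval applies to fitness and weight only. The explicit t0–t3 focus is written under question 2; for question 1 it follows only from the 0–3 time coding.
- **That season or the pandemic shifts everyone the same way.** Entry from January to October makes seasonal shifts partly cancel, and the pandemic is a before/after contrast only for early entrants. The documents report no effect of it on activity or weight.
- **That the percentages above are the trial's false-positive rate.** They are the power to detect an assumed drift. The planned main analysis is also a mixed model under intention to treat with imputation, not a paired test in completers.

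**Conclusion.** The point holds for the fitness and weight trials. Research question 1 is worded causally and answered by a within-arm change that this design cannot attribute to the program. That conclusion follows from the structure alone and needs no assumed drift.

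The size of the possible error is unknown. The illustration shows only that it need not be large: about 0.12 SD observed at r = 0.5, or about 0.10 SD at r = 0.7, with 253 completers per arm. Season alone would probably have to be strong to produce this after averaging over entry dates. Motivation at entry, natural course and regression to the mean do not cancel in that way, but the documents give no figure for them.

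For the smoking trial the point shrinks to wording: question 1 predicts significant improvement for each program, while the analysis has moved to the between-group difference. Hypothesis 2, its type I error and the sample size are untouched. The change is worth making before results are written up.

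**What to change.** - Restate research question 1 as a description: mean change in each arm for fitness and weight, and abstinence proportion in each arm for smoking, with 95% confidence intervals and without an effectiveness claim or confirmatory test.
- State that conclusions about effectiveness rest on the randomized contrast: γ11 (hypothesis 2) for fitness and weight, and the between-group difference already named for smoking.
- Optionally, tabulate within-arm change by calendar quarter of t0 and by entry before or after March 2020. Questionnaire timing must already be tracked, since Data management describes blocking questionnaires after eight weeks.

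This costs a change of wording and at most one descriptive table, with no new data and no change in sample size. The real price is that the sponsor gives up a standalone effect claim for each program. The randomized comparison can show only the advantage of the interactive over the non-interactive version.
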